### Interim analyses {21b}

The team will undertake basic descriptive analyses of baseline data from each target sample. The team also will undertake psychometric analysis (exploratory factor analysis, confirmatory factor analysis, and multiple-group confirmatory factor analysis) of each scale-related item set to assess the measurement invariance if item sets across universities, IS groups, and study wave. The study team will present interim results to the study’s Data Safety and Monitoring Board (DSMB) biannually during data collection, and as needed, to the DSMB, Emory IRB, and sponsor if a participant reports unmanageable distress (see Composition of the data monitoring committee, its role, and reporting structure, below). The DSMB and Emory IRB will make independent determinations about the need to terminate the trial, which will be shared with the sponsor for review and a final decision.

### Methods for additional analyses (e.g. subgroup analyses) {20b}

Each participating university will be invited to propose subgroup analyses of the data collected at their respective university. Proposals for these analyses will be submitted to the SCALE Steering Committee and reviewed on a rolling basis (**Appendix**).

### Methods in analysis to handle protocol non-adherence and any statistical methods to handle missing data {20c}

To address protocol non-adherence, we will evaluate the balance between study arms (HIS and LIS groups) based on student responses regarding any modifications to program delivery. If necessary, we will adjust for these modifications in our analysis to reduce potential bias. Moreover, we will conduct a per-protocol analysis, including only those participants who adhered to the protocol. Comparing the results of these analyses with analyses of all participants will provide insights into the impact of non-adherence.

Inadvertent missingness will be minimized at the data collection stage by pre-programming the REDCap data system to inform the participant of any missing responses and to invite them to complete their responses before proceeding to the next survey page. Sensitivity analyses will also be conducted, with missing data imputed under the assumption of missingness at random.

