**Methods:**

We will randomize six medical universities in North, Central, and South Vietnam to deliver GlobalConsent using two different packages of implementation strategies that vary in intensity. Higher-intensity strategies will include greater 1) pre- and post-implementation engagement with university leaders and faculty, and 2) greater pre-implementation outreach, follow-up, and incentives for students to promote engagement and completion of GlobalConsent. Higher intensity universities will receive additional training and support for their added activities. We will compare implementation drivers and outcomes, intervention effectiveness, and cost-effectiveness across the two implementation bundles. Our mixed-methods comparative interrupted time-series design includes 1) qualitative interviews and quantitative surveys with university leaders and implementation teams to assess implementation barriers and facilitators; 2) repeated surveys with leaders and faculty, implementation teams, and male students to assess multilevel implementation drivers and outcomes, 3) repeated surveys with male students to assess behavioral outcomes (sexual violence and intervening behavior) and mediating variables (knowledge, attitudes, affect, and capacities), and 4) time diaries and cost tracking to assess cost effectiveness of the two implementation-strategies bundles.

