#### Engage potential consumers (university-student users of GlobalConsent).

Students only in the HIS group additionally will receive: educational outreach in a pre-implementation in-person orientation to GlobalConsent covering similar topics and three monthly one-hour learning sessions during implementation in which technical questions about program access or progression can be addressed; more intensive intervention to enhance adherence with more frequent email/SMS completion reminders (weekly versus every two weeks for 12 weeks); and demand generation with an option to enter a lottery to win prizes upon program completion.

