Longitudinal focus group discussions (FGDs) will entail four discussions with each of six groups of 5–8 [57] implementation team members (one group per university; 24 FGDs total). These FGDs will provide detailed, near-real-time data on the project’s dynamic implementation context, including features of the implementation setting; modifications to GlobalConsent or implementation plans; changes in the university, local, regional, or national context that may affect implementation; and team sense-making and learning [58]. The FGD guide [46] includes open-ended questions aligned to FRAME; the rationale, timing, and guidance for each question; and probes about the use of core implementation strategies (**Appendix**). Some questions in the FGD guide are like those in the KII guide to facilitate triangulation of the data during analysis.

A brief checklist will be added at the end of every program module of GlobalConsent (**Appendix**). This checklist will be based on the Modifications and Adaptations Checklist [59, 60], a coding scheme for recording modifications to evidence-based interventions. The checklist will ask participants to self-report any modifications they made to planned use of GlobalConsent. As students cannot skip segments or modules in GlobalConsent, the checklist will focus on the following major modifications: 1) device used to view each module of GlobalConsent, 2) percentage of module watched, 3) number of sessions required to watch the module, 4) whether or not they watched part or all of each module mor than once; 5) ‘drift’ by multi-tasking or doing other things while a module was open, 6) ‘drift’ by stepping away from the computer or mobile device while a module was open, 7) extent of satisfaction with the content of the module, and 8) any comments about the module.

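### The non-adherence plan lets arm differences in programme use trigger adjustment of the HIS–LIS comparison, although programme use is what HIS is meant to change; adjusting removes the part of the HIS effect that runs through it

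*Protocol article*

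**What the plan says.** Section {20c} of the Protocol article handles non-adherence in four steps.

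- A balance check: "we will evaluate the balance between study arms (HIS and LIS groups) based on student responses regarding any modifications to program delivery".
- A consequence: "If necessary, we will adjust for these modifications in our analysis to reduce potential bias".
- An additional analysis: "we will conduct a per-protocol analysis, including only those participants who adhered to the protocol".
- A reading of the results: "Comparing the results of these analyses with analyses of all participants will provide insights into the impact of non-adherence".

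The student-reported modifications are described under Outcomes {12}, Aim 1: "A brief checklist will be added at the end of every program module of GlobalConsent". Its items include "2) percentage of module watched, 3) number of sessions required to watch the module", along with device, repeat viewing, multitasking, stepping away, satisfaction and comments.

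The Abstract says that the HIS bundle includes "greater pre-implementation outreach, follow-up, and incentives for students to promote engagement and completion of GlobalConsent". The Intervention description {11a} lists, for HIS students only, "more intensive intervention to enhance adherence with more frequent email/SMS completion reminders" (weekly against every two weeks), an in-person orientation, monthly learning sessions and a lottery on completion. Under Outcomes {12}, Aim 2, completing the programme is itself an implementation outcome (penetration). Objectives {7} expects implementation outcomes to be better under HIS.

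**The concern.** Both arms deliver the same web programme; only the strategies around it differ. If HIS gets students to watch more of it and drift less, the arms will differ on the checklist because HIS worked. Section {20c} treats that difference as a possible source of bias and lets it trigger adjustment. A variable that is measured after randomisation and is affected by the allocation cannot confound the allocation. It lies on the path from HIS to behaviour, so conditioning on it biases the estimate of the total HIS effect. The rule is also most likely to be invoked when HIS succeeds in raising engagement.

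The adherers-only contrast conditions on the same kind of variable. It also compares groups that the two bundles are designed to select differently, because a student who adheres with few reminders is not the same kind of student as one who adheres with many. The gap between that contrast and the all-participant result therefore mixes loss of the mediated effect with selection.

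The Aim 3 contrast is at stake, and so is Aim 4, whose net effectiveness is defined by the same HIS-minus-LIS difference.

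**Working it through.** **1. The plan's own figures** (Power for analyses of student data, Aim 3). 4,776 × 0.80 × 0.90 = 3,438.7, which matches the stated ~3,439. 0.65 + 0.35/2 = 0.825, which matches the stated IRR. The power of .91 cannot be reproduced, because the mean count and the random-intercept variance are not given. Taken as two-sided, it implies a standard error for the log IRR of |ln 0.825| / (1.960 + 1.341) = 0.1924 / 3.301 = 0.058. The concern is about what is conditioned on, so nothing below depends on that power figure.

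**2. Direct arithmetic.** Let m be the share of the log-scale effect that passes through programme use. If nothing else links use and behaviour, adjusting for use leaves IRR_adj = 0.825^(1 − m):

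- m = 0: 0.825
- m = 0.50: 0.908
- m = 0.75: 0.953
- m = 1: 1.000

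**3. Simulation check.** Arm affects share watched, which affects a Poisson count, with the total IRR held at 0.825 and n = 3,438. There were 200 runs per setting, at individual level without university clustering. The following are assumptions that the documents do not give: baseline mean 0.5 or 1.0 acts; typical share watched 50% in LIS and 75% in HIS; adherer = at least 80% watched. Each cell shows the IRR for baseline mean 0.5 / 1.0.

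| m | All participants, unadjusted | Adjusted for share watched | Adherers only |
|---|---|---|---|
| 0% | 0.830 / 0.826 | 0.829 / 0.825 | 0.829 / 0.818 |
| 50% | 0.824 / 0.825 | 0.909 / 0.910 | 0.897 / 0.900 |
| 75% | 0.823 / 0.821 | 0.953 / 0.951 | 0.953 / 0.939 |
| 100% | 0.823 / 0.820 | 1.002 / 0.995 | 0.986 / 0.985 |

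The unadjusted comparison recovers the design value throughout, and the adjusted column follows the formula in step 2. At m = 100% the share of runs significant at .05 falls from 0.85 / 0.985 unadjusted to 0.04 / 0.04 adjusted.

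**4. Adding selection.** Suppose an unmeasured trait makes students both more likely to watch and less likely to offend (assumed: +1.0 on the logit of share watched and −0.3 on the log rate, per standard deviation). The unadjusted IRR stays at 0.82–0.83. At m = 100% the adjusted IRR becomes 1.17 / 1.18 and the adherers-only IRR 1.13 / 1.12, so the direction reverses. At m = 0 they are 0.97 / 0.97 and 0.94 / 0.94, so both contrasts are distorted even without mediation.

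**The case against.** The plan is more cautious than a quick reading suggests. The adjustment applies only if judged necessary, the per-protocol analysis is an addition, and the all-participant analysis is kept as the comparator. The basic Aim 3 model in section {20a} contains university, time and period terms and no adherence covariate. A reader might infer that the trial will judge HIS on adherers only, or that the main model will be adjusted; the documents support neither. All of this stands. What it does not settle is scope: section {20c} speaks of the analysis without confining the adjustment to a sensitivity analysis, and it presents the adjustment as a reduction of bias.

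A reader might also infer that these steps would wipe out the HIS effect. One can take 0.65 as the full programme ratio and assume 80% against 40% completion. The all-participant IRR is then (1 − 0.35 × 0.8)/(1 − 0.35 × 0.4) = 0.72/0.86 = 0.84, and the completers-only IRR is 0.65/0.65 = 1.00. That 1.00 is built in: it follows for any completion rates once the whole effect is assumed to run through completion. The protocol gives no completion rates and does not label 0.65 as the programme effect. HIS also works through leaders and faculty, so other routes are open.

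Some checklist items, such as device, are not obvious mediators. Because students cannot skip segments or modules, the percentage watched may vary little among those who answer, in which case adjusting for that item would change little.

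It is tempting to add that adjustment would drop students who never reach the end of a module. That is plausible but inferred. Table 4 expects about 3,821 checklist respondents, equal to all expected participants (4,776 × 0.80), and imputation is planned as a sensitivity analysis without saying whether it covers these items.

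The protocol does not define adherence for the per-protocol set, but that can properly be left to an analysis plan and is not held against it here.

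**Conclusion.** The concern holds in this form. Section {20c} permits the HIS–LIS analysis to be adjusted for programme-use items that are measured after randomisation and that HIS is designed to influence, and the reason it gives, bias reduction, is wrong for the total HIS effect. The estimate is attenuated in proportion to the mediated share: from 0.825 to about 0.91 at 50%, 0.95 at 75% and 1.00 at 100%, with no change at 0%. These figures assume that no unmeasured factor links programme use and behaviour. With such a factor the estimate can move further, even past 1. The mediation shares, exposure levels and baseline means are assumptions, so the range is illustrative and not a forecast.

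Full loss of the effect is the extreme case, and the documents do not show that it would occur. The per-protocol contrast is supplementary, but its gap from the all-participant result cannot be read simply as the impact of non-adherence.

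**What to change.** In section {20c}:

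- Delete the sentence allowing adjustment for programme-use modifications, or confine it to an analysis labelled as mediation or exploratory, with its assumptions stated.
- State that the comparison of all participants as randomised, unadjusted for programme use, is the estimate of HIS versus LIS for Aim 3 and for the Aim 4 cost-effectiveness ratio.
- Report the checklist items by arm as descriptive implementation results.
- Keep the per-protocol analysis only as supportive, label it as not estimating the HIS effect, and reword the sentence on what its gap from the all-participant result shows.

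The cost is a few sentences of rewording, with no new data and no change to the sample. A mediation analysis (HIS to programme use to behaviour) is optional and would use data already being collected.

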### Plans to give access to the full protocol, participant level-data and statistical code {31c}

The full protocol here, including study forms, will be made available through peer-reviewed publication. Participant-level data will be made available through the National Institute of Mental Health Data Archive (NDA) and Emory dataverse—Emory’s open-data repository—to support the preservation, discoverability, and accessibility of data that team members in this project produce. At the project’s completion, upon publishing the main findings, we will make study documentation, data dictionaries, and the final, cleaned, recoded, and de-identified data available through the NDA and Emory’s dataverse. We will develop a formal data-sharing agreement between key personnel at Emory University, the Center for Creative Initiatives in Health and Population (CCIHP), Georgia State University (GSU), and participating universities. This data sharing plan will describe the subsets of data to be made available to participating universities during the project period (**Appendix**). The data sharing agreement with participating universities will provide standard procedures for applications to use the data and project guidelines for publication. Statistical code for analyses will be made available upon reasonable request to the corresponding author of project-related publications.

## Oversight and monitoring

### Composition of the coordinating centre and trial steering committee {5d}

The overall structure of the study team will include a central Steering Committee comprised of key personnel, each of whom is responsible for one or more specific aims and/or local imple-mentation of the project (**Figure 3**). The principal investigator (PI) at Emory University will chair the Steering Committee and will provide leadership for Specific Aims 1 and 3, related to implementation fidelity and effectiveness. The site-PIs at CCIHP and at Georgia State University will provide leadership for Specific Aim 2 on implementation drivers and outcomes. The health economist co-investigator at Georgia State University will provide leadership for Specific Aim 4 on cost-effectiveness and will provide overall statistical guidance to the study team. The site-PI and co-investigator at CCIHP will provide input on the research design and will lead external implementation support to participating universities in Vietnam. The IT company contracted in Vietnam will deliver the GlobalConsent program to participating students, will send reminders to complete each module, and will track adherence metrics at the student participant level. The Steering Committee will meet weekly to design, implement, and evaluate this initiative. A project coordinator / data analyst at Emory University will support the Steering Committee and will receive opportunities for professional development throughout the initiative. Pre-doctoral students at Emory University and Georgia State University will support all aspects of the research, from design to implementation and analysis and will receive capacity strengthening in research and opportunities for professional development.

### Composition of the data monitoring committee, its role and reporting structure {21a}

#### Roles and membership.

An independent Data and Safety Monitoring Board (DSMB) will include three experts in 1) implementation science, 2) sexual violence prevention, and 3) biostatistics. This DSMB is charged with reviewing study data for quality and integrity, adherence to the protocol, participant safety, study conduct and progress, and making determinations regarding study continuations, modifications, and suspensions/terminations. The monitoring responsibilities of the DSMB will enhance, but will not replace, the monitoring responsibilities of the Principal Investigator (PI) and the IRBs for this project. The PI and study team retain responsibility for real-time management of the study.

#### Independence of DSMB members.

DSMB members will be independent from any professional or financial conflict of interest (COI) with the research project and/or study investigators. Independence ensures that competing interests do not unduly influence the DSMB and supports objectivity that enhances the safety of participants and the integrity of the trial data. Potential DSMB members will provide the NIMH with qualifications and a COI statement indicating that members have no direct involvement with the study or COI with the investigators conducting the study. DSMB members may be affiliated with the investigator’s institution or other participating sites, but cannot be a scientific collaborator or co-author, supervisor, mentor/mentee, subordinate of the investigators, or a member of the investigator’s institutional department within the last three years. DSMB fees will be provided, per NIH and Institutional Policies.

#### Responsibilities and review.

The DSMB will review the DSMP and study protocol before the first participant’s enrollment to establish a charter that clarifies what data points will be monitored, how they will be monitored, and the monitoring schedule. The DSMB review will include, at a minimum: enrollment data, safety data, and data integrity. As this study is blinded, the DSMB may be blinded or unblinded to the intervention assignment but will be able to be unblinded if needed.

#### Metrics for review.

The study team will provide descriptive statistics for the DSMB’s review at each of its meetings. Descriptives will cover questions from the following survey modules for male students and will include information about missingness/non-response.

Demographics (once at baseline)Knowledge about sexual violence (from each survey wave)Knowledge about sexual consent (from each survey wave)Rape Myths (from each survey wave)Skills to engage in healthy communication (from each survey wave)Rape empathy (from each survey wave)Readiness to intervene (from each survey wave)Bystander intervention strategies (from each survey wave)Sexual Experiences (from each survey wave)Single question on distress (SRQ-20 item 6)

In addition to the above enrollment and safety data, the study team will provide data to the DSMB on the following study-related variables from male students:

Participation rates in the survey, by universityRetention rates in the survey at each wave, by universityParticipation rates in the program, by universityRetention rates in the program, by university

#### Review schedule and monitoring reports.

The DSMB meeting/review schedule will be commensurate with the level of risk involved with the study but will occur no less than once per year. Additional reports may be requested, and additional meetings may be called as needed to address issues regarding participant safety. Members of the investigative team may be present for the open portion of a DSMB meeting, but not for the closed deliberations or the vote to recommend continuation, suspension, or termination of the study. The DSMB will issue a monitoring report to the PI after each review/meeting. This report will include any significant actions taken and the final recommendation(s) regarding the study’s continuation. These reports will be submitted to National Institute of Mental Health (NIMH) program staff in the annual progress report. The planned frequency of meetings is annually in 2023, 2026, 2027 before and after the period of data collection and program implementation; and twice annually in 2024 and 2025, during the period of data collection and program implementation.

### Adverse event reporting and harms {22}

For this study, standard adverse-event definitions are used. An adverse event (AE) refers to any unfavorable and unintended sign (including distress), symptom, or disease temporally associated with the use of a medical treatment or procedure, regardless of whether it is considered related to participation in the GlobalConsent program. A serious adverse event (SAE) is any AE that is life-threatening or results in death, an event requiring inpatient hospitalization or prolongation of existing hospitalization, or persistent or significant disability/incapacity.

Adverse events are graded as mild, moderate, or severe. A mild AE is an experience that is transient and requires no special treatment or intervention. The experience does not generally interfere with usual daily activities. This experience includes transient laboratory test alterations. A moderate AE is an experience that is alleviated with simple therapeutic treatments. The experience impacts usual daily activities. This experience includes laboratory test alterations indicating injury, but without long-term risk. A severe AE is an experience that requires therapeutic intervention. The experience interrupts usual daily activities. If hospitalization (or prolongation of hospitalization) is required for treatment, it becomes a SAE.

The study uses a standard adverse-event attribution scale. Not related means that the AE clearly is not related to the study procedures (i.e., another cause of the event is most plausible and/or a clinically plausible temporal sequence is inconsistent with the onset of the event). Possibly related means that an event that follows a reasonable temporal sequence from the initiation of study procedures, but that could readily have been produced by several other factors. Related means that the AE is clearly related to the study procedures.

A comprehensive list of resources will be made available to every participant toward the end of every survey to ensure that all participants have access to confidential care. In addition, adverse events among students who are receiving the GlobalConsent program will be identified with a series of self-report questions at the end of every survey. These questions will identify the level of distress the participant is experiencing in the moment and its self-reported manageability. Any participant who reports extreme distress (level 10 on a scale of 1–10) or any level of distress that they identify as “not at all manageable” will be given a contact number for an experienced professional for immediate support. Such participants also will be invited to have a non-study staff member connect them with an experienced professional for a confidential assessment and then appropriate referrals.

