### Criteria for discontinuing or modifying allocated interventions {11b}

CCIHP will encourage adherence to the implementation plan of the LIS and HIS groups in response to any questions that are posted to the GlobalConsent website regarding deviations to the implementation plan. CCIHP also will encourage adherence to the implementation plan of the HIS group in its regular consultative meetings, when it provides technical support. The study team will conduct regular focus group discussions with implementation teams to monitor modifications to implementation strategies that LIS and HIS implementation teams may apply (Aim 1). The decision to discontinue a student’s participation in GlobalConsent will be made based on an adverse events protocol that is described elsewhere in this study protocol.

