#### First-year undergraduate male students (Aims 1 and 3).

All eligible students will be invited to participate in 6 six-monthly surveys and the GlobalConsent program. For the LIS and HIS groups, implementation team members will send a standard email invitation to all eligible men with a description of the GlobalConsent program, a description of the study, and an invitation to participate. They will separately receive a secure REDCap link to the online informed consent form, and if completed, the online survey (Table 6). For the HIS group, internal facilitators will organize an orientation session for all eligible male students to describe these elements in person and to answer any questions about participation. All eligible participants will be informed during the online informed consent process that they will be compensated $5.50 in average for completing each survey assessment, for a total compensation of $33 for completing all six assessments. All eligible participants also will be informed during the online informed consent process that they will be eligible to enroll in a lottery to receive a prize (e.g., smartphone) after completing three survey assessments, and that they will be eligible to enroll in a second lottery to receive a prize (e.g., smartphone) after completing six survey assessments. All eligible participants in the HIS group will be informed about this compensation schedule during the recruitment orientation meeting.

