#### Survey-based data collection (Aim 1 checklist; Aims 2–3).

Survey-based data from all target populations will be collected via REDCap [49], a HIPAA-compliant, web-based data system that allows for the secure collection, transfer, storage, and analysis of study data. Customized surveys will be piloted with individuals like the focal populations but at non-study universities to gauge acceptability, inform final revisions, and assess timings to minimize respondent burden (e.g., 10–15 minutes for each leader, faculty, and implementation team survey; 16 minutes for each student survey). The survey implementation protocol described, above, under “Recruitment” will be followed for at each survey wave for faculty, implementation teams, and students to maximize their participation at baseline (~80%) and retention at endline (~90%), based on prior experience surveying students in Vietnam [51].

Measurement time points will vary for each target sample, according to the project timeline (Figure 2). Leaders will be assessed twice, once before and once after implementation. Implementation teams will be assessed quantitatively at four time points: once before the start of any implementation activities, and once immediately before, during, and after implementation of GlobalConsent. Other data on the implementation will come from administrative records collected by the IT company that is responsible for delivering GlobalConsent. Faculty will complete one assessment before implementation (Year 1) and two after the planned 12-week delivery period of GlobalConsent (Years 3, 5). Three surveys will be administered to students at six-month intervals before the planned 12-week delivery period of GlobalConsent, and three six-monthly surveys will be administered at the same interval after implementation, for a total of six assessments. At each occasion, we will send to students’ smartphones an encrypted link to a REDCap survey with ~189 questions measuring two primary behavioral outcomes and seven cognitive/knowledge, attitudinal/belief, affective, and capacity-related secondary outcomes validated in the efficacy trial [33, 50, 51] (Table 6). Secondary outcomes that are included align with our theory of change (Figure 1) and showed evidence of mediation in the trial [50]. A short modification checklist of 5–10 questions will be administered at the end of each GlobalConsent program module to understand participants’ engagement and satisfaction with the module (Table 4).

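### As the text reads, no distress question is scheduled during the 12-week programme, so the adverse-event rule for stopping a student has no scheduled trigger while he is in it

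*Protocol article*

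**What the plan says.** Adverse event reporting and harms {22} gives the means of detection: "adverse events among students who are receiving the GlobalConsent program will be identified with a series of self-report questions at the end of every survey". The questions ask about distress at the time of answering and its manageability. Provisions for post-trial care {30} describes the same trigger near the end of each survey: distress scored 1 to 10 and manageability scored 0 to 2, with a flag at a distress score of 10 or at the worst manageability category.

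The calendar is in two places. Recruitment {15} states: "All eligible students will be invited to participate in 6 six-monthly surveys and the GlobalConsent program". Plans for assessment and collection of outcomes {18a} places the first half of the series: "Three surveys will be administered to students at six-month intervals before the planned 12-week delivery period of GlobalConsent". For the second half, the same sentence adds that "three six-monthly surveys will be administered at the same interval after implementation".

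During delivery, students complete a checklist after each module. Section {18a} says that it "will be administered at the end of each GlobalConsent program module to understand participants’ engagement and satisfaction with the module". Outcomes {12} introduces its content: "As students cannot skip segments or modules in GlobalConsent, the checklist will focus on the following major modifications". Eight topics follow: device, share of the module watched, number of sessions, repeat viewing, two kinds of inattention, satisfaction, and free comments.

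Criteria for discontinuing or modifying allocated interventions {11b} provides that the decision to end a student's "participation in GlobalConsent will be made based on an adverse events protocol that is described elsewhere in this study protocol". The section on expected adverse events lists mild distress from taking part, including through recall of incidents of sexual violence.

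**The concern.** Three provisions, each reasonable alone, do not fit together. Detection is meant for students who are receiving the programme. The only stated detection points are the surveys, and the surveys come before or after the programme. The stopping rule depends on what is detected. Waves 1 to 3 precede exposure, and waves 4 to 6 come when planned delivery is over and little or nothing is left to stop.

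Two things are at stake. A student who is badly distressed by a module has no scheduled occasion to say so while stopping is still possible, and so no scheduled entry to the referral pathway. In addition, because the questions have no recall period, distress that arose and settled during delivery would not be recorded at wave 4. A low count of programme-related events would then partly reflect when students were asked.

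**Working it through.** This is schedule arithmetic; no power or sample-size formula applies.

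**Inputs**
- Student surveys: 3 before and 3 after delivery, six-monthly ({18a}).
- Planned delivery: 12 weeks ({18a}); six modules (Abstract), each to be completed within two weeks (training of implementation teams, under {6b}).
- Time axis of the student model: 10 quarters ({20a}, Aim 3).
- Checklist: eight listed topics ({12}); 5 to 10 questions ({18a}).
- Start of delivery relative to wave 3: not given in the visible text (Figure 2 is not shown), so a range is used.

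**Reproducing the plan's figures.** 3 + 3 = 6 assessments, as stated. Six-monthly spacing gives months 0, 6, 12, 18, 24 and 30: 5 gaps × 2 quarters = 10 quarters, which agrees with the model's time axis. Delivery: 6 modules × 2 weeks = 12 weeks, as stated.

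**Distress questions inside delivery.** Waves at or before the start: 3. Waves at or after the end: 3. Waves inside: 6 − 3 − 3 = 0.

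**Time to the first question after exposure**, taking waves 3 and 4 as six months (about 26 weeks) apart. Slack outside delivery = 26 − 12 = 14 weeks. If delivery starts *s* weeks after wave 3, with *s* from 0 to 14:
- module 1 opening to wave 4 = 26 − *s*
- end of delivery to wave 4 = 14 − *s*

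| *s* (weeks) | Module 1 opens to wave 4 | Delivery ends to wave 4 |
|---|---|---|
| 0 | 26 | 14 |
| 7 | 19 | 7 |
| 14 | 12 | 0 |

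The range is 12 to 26 weeks from the opening of module 1. The wording on the post-delivery interval could also mean that wave 4 falls six months after delivery ends, giving 12 + 26 = 38 weeks. The six waves would then span at least 4 + 38/13 + 4 = 10.9 quarters, so the first reading fits the stated 10 quarters better and is the one used here.

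**Reach of the other wave 4 measures** (Table 6). The anxiety, depression and cross-cutting items look back two weeks, and the disability scale 30 days (30/7 = 4.3 weeks). They reach into delivery only if wave 4 falls within about 2 or 4.3 weeks of its end, against a possible gap of 0 to 14 weeks. They are also not the stated adverse-event trigger.

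**Room on the checklist.** 8 listed topics + 2 distress items = 10, the upper end of the stated 5 to 10, if each topic takes one question.

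**Effect of adding the items.** Scheduled checks during delivery rise from 0 to 6 for a student who completes every module, about one every two weeks if he keeps to the schedule.

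**The case against.** The best reply is that the module checklist is itself a survey. Strategies to improve adherence {11c} calls it a short survey, the headings in {18a} and Confidentiality {27} group it with survey data, and Data management {19} places it in the same REDCap system that raises the flag. Section {30} also applies case management to students in the programme as well as at each wave. If every survey includes the module form, distress is asked during delivery. The form sits in an Appendix that is not shown, the list in {12} is not said to be exhaustive, and two more items would fit the stated length. This lowers certainty. It does not remove the mismatch, because neither the listed topics nor the stated purpose of engagement and satisfaction includes distress. If the wider reading is intended, the text should say so.

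The second reply is that the harm is modest. The expected event is mild distress, which {22} defines as transient and needing no special treatment, and the flag requires the most extreme answer on one of two scales. The expected event would ordinarily not raise a flag even if students were asked after every module. That stands, and it limits how much weight the point can bear.

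Partial cover also exists. The checklist has an open-comment item. Every survey gives a resource list. A flag at wave 3 could stop a student from starting. A late finisher could still be in the programme at wave 4. A student may volunteer a report. The wave 4 mental health measures look back two weeks or 30 days. None of these is the stated means of identification, but together they mean that students are not without recourse.

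The list of descriptives for the monitoring board does not settle the matter. It names no checklist item, but it does not name the 1-to-10 distress or the manageability item either.

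**Conclusion.** The point holds as a matter of safety-assessment timing. On the visible text, 0 of the 6 scheduled distress assessments fall inside the 12-week delivery, so the rule for discontinuing a student has no scheduled input while he is in the programme. If waves 3 and 4 are six months apart, the first post-exposure question comes about 12 to 26 weeks after module 1 opens and asks only about the present.

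This rests on two assumptions: that the Appendix checklist matches the topics listed in {12}, and that the distress items appear only at the survey waves.

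A reader might infer that serious programme-related distress will go undetected, or that students are unprotected during delivery. The documents do not support that. They give no event rate, so no count of missed events can be given; the expected event is mild; and the unscheduled routes above remain open. A reader might also set the wait for wave 4 against the few days planned for expert contact after a flag. One is a delay before detection and the other a response time after it, so a ratio of the two says nothing useful. The point is a cheap and worthwhile improvement, and it affects no outcome analysis.

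**What to change.** First check the Appendix form. If it already carries the distress and manageability items, only the wording of {22} and {12} needs correcting. If not:

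- Add the two existing items (distress 1 to 10, manageability 0 to 2) to the end-of-module checklist, with the same thresholds, emergency number and referral offer.
- Reword {22} so that adverse events are identified at each survey wave and after each module.
- State in {11b} that a flag raised after a module is referred for the discontinuation decision.
- Leave the survey-wave questions, referral steps and reporting as they are.

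The cost is a slightly longer checklist, possibly more referrals and event reports, and one ethics amendment. No new survey wave is needed. One gap remains: a student who leaves part-way through a module does not reach the checklist and is not asked until the next survey.
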